**Methods and analysis:**

This longitudinal between-subjects study will recruit 60 participants who will each be randomly assigned to receive either active or sham tDCS. Participants will undergo 5 sessions, each spaced approximately one week apart. In session, they will receive 20 minutes of (active/sham) 1.5mA anodal stimulation over the right dorsolateral prefrontal cortex while receiving training in cognitive reappraisal. Primary outcomes include changes in cannabis use during the study, changes in electroencephalogram brain activity when viewing cannabis cues, and changes in cannabis craving intensity.

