The present study seeks to evaluate the efficacy of tDCS to the right dlPFC paired with training in cognitive reappraisal in improving craving regulation and reducing cannabis use in individuals with CUD. Specifically, we hypothesize that participants who receive active versus sham tDCS will have 1) greater reductions in daily cannabis use, 2) changes in neural correlates of EEG features associated with craving (e.g., relatively diminished LPP amplitude and increased delta power) while viewing cannabis cues, and 3) greater reductions in cannabis craving. We also hypothesize tDCS-related increases in neural correlates of EEG features associated with regulation (e.g., frontal theta power).

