## Materials and methods

### Study design

This protocol is written in accordance with the Standard Protocol Items: Recommendations for Interventional Trials (SPIRIT) reporting template [36]. The present study will utilize a randomized design where participants are allocated to either an active stimulation condition or a sham control condition in a 1:1 ratio. To ensure randomization of active/sham administration across sexes, this 1:1 ratio is allocated within males and females separately. To minimize bias, both study participants and research staff running study visits will be blinded to the participant’s assigned experimental condition. This entails five weekly visits (baseline and four weekly visits thereafter), during which participants will undergo a 20-minute session of (active/sham) tDCS and reappraisal training each week. Participants will complete a self-report measure of cannabis craving [37] immediately before and after each tDCS and reappraisal training session. Before the first tDCS session on the first visit and after the last tDCS session on the fifth visit, participants will complete the Regulation of Craving (ROC) task [3,38], during which EEG activity will be recorded. In addition to the in-person study visits, beginning after the first study visit and ending at the last visit, participants will provide information on past 24-hour cannabis use through a daily survey delivered via short message services (SMS).

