### Participant timeline

The timeline for participants is presented in Fig 1. After participant eligibility is determined, participants will be invited to the first study visit (V1), where they will provide informed consent for participation, complete baseline questionnaires, complete a pre-intervention ROC task while EEG activity is recorded, and then receive the first session of tDCS and reappraisal training. Participants will also complete the Marijuana Craving Questionnaire (MCQ) [37] before and after the intervention. This visit should take about three hours.

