**Fig 1 pone.0328205.g001:**
[figure not shown]
Notes: AECS: Anticipated Effects of Cannabis Scale; CFCS: Consideration for Future Consequences Scale; CUDIT-R: Cannabis Use Disorder Identification Test, Revised Edition; ERQ: Emotion Regulation Questionnaire; GAD-7: Generalized Anxiety Scale; PHQ-9: Patient Health Questionnaire; MCQ: Marijuana Craving Questionnaire; SRHI: Self-Report Habit Index; ROC task: Regulation of craving task. TDCS: 20 minutes of 1.5mA active/shame transcranial direct current stimulation; TAS-20: Toronto Alexithymia Scale-20; TEX-Q: Treatment Expectations Questionnaire; WHODAS 2.0: World Health Organization Disability Assessment Schedule 2. Note that questionnaire completion and the ROC task with EEG recording occur before the intervention session on V1, and after the intervention session on V5. * Daily cannabis use surveys are sent to each participant for 28 days following enrolment.

Study visits two through four (V2-V4) will be shorter visits during which participants only receive tDCS and reappraisal training and complete the MCQ before and after the intervention. Study visit five (V5) will consist of the same intervention administration and assessment of cannabis cravings as all previous visits. Additionally, participants will complete a post-intervention ROC task while EEG activity is recorded followed by post-intervention questionnaires.

At every appointment, research staff will assess for any adverse events (AEs) and record those reported by each participant in their study record. The study investigators will be responsible for determining the severity of AEs and their relationship to study procedures. Following any severe AEs that are possibly, probably, or definitely related to study procedures, research staff will consult the investigative team to determine if it is appropriate to continue study procedures. Although we do not expect any serious adverse events (SAEs), any participant who reports an SAE will be withdrawn from the trial and referred for appropriate follow-up care. Additionally, following the first study visit and until the end of the last study visit, participants will receive a once-daily survey asking about the amount of cannabis used and the form (e.g., smoked, vaped, edibles) of cannabis used in the past 24-hour window. In this survey, participants will also rate how the amount of cannabis used compares to the amount of cannabis they would typically use.

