### Data analysis

Data collected throughout this study will primarily be analyzed using SPSS software. To address the first aim of the study, reductions in cannabis use, as reported by research participants through the daily-administered REDCap surveys, will be analyzed using a multilevel modeling strategy. Multilevel modeling with maximum likelihood estimation for missing data will be used to conduct a linear analysis of daily use of cannabis using a nested hierarchical structure with both between- and within-subject predictors. The main effects of Group (i.e., stimulation versus sham) and Time, as well as the Group x Time interaction will be the primary fixed effects of interest. Daily use of cannabis will be compared across the study weeks, and multilevel models will be constructed to examine the slopes of longitudinal data across the weeks.

Statistical analysis of the EEG correlates of craving and regulation will be conducted using Netstation pipelines for ERPs and Matlab scripts for oscillatory power. Data will be filtered offline at 0.1–30 Hz. Ocular artifact correction will be performed on the mean amplitudes of each component with a specified timeframe. The components of interest for this analysis will consist of the P300, the LPP, and frontal theta power. These variables will be compared across Group (i.e., stimulation versus sham), Condition (i.e., LOOK or NEGATIVE), and Time (V1 and V5) in a series of ANOVAs. We hypothesize that active stimulation will result in heightened amplitude of the early LPP in the LATER condition, as regulation of craving is hypothesized to be enhanced, and diminished amplitude of the late LPP in the LATER condition, as arousal related to craving is hypothesized to be reduced. Further, we expect that frontal theta power will be enhanced after tDCS stimulation during the LATER condition.

For the third primary outcome, craving will be measured both pre- and post-tDCS using the MCQ [37], and active and sham groups will be compared via an ANOVA (Group x Condition x Time). Additionally, self-reported cravings elicited by cannabis images in the ROC task in both the LOOK and NEGATIVE conditions are rated on a 5-point Likert scale at baseline and post-treatment. These data will be averaged across trials and compared between groups via an ANOVA (Group x Condition x Time).

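### The first primary outcome is called a reduction in daily cannabis use, but use is first recorded after the first tDCS session, so change from a pre-treatment level cannot be estimated

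*Protocol article*

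**What the plan says.** **Outcome.** The Introduction predicts that "participants who receive active versus sham tDCS will have 1) greater reductions in daily cannabis use". The abstract uses the same idea: "Primary outcomes include changes in cannabis use during the study". The Data analysis section again speaks of reductions in use.

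**When use is recorded.** Study design has the daily survey "beginning after the first study visit and ending at the last visit, participants will provide information on past 24-hour cannabis use". Participant timeline repeats this ("following the first study visit and until the end of the last study visit, participants will receive a once-daily survey"), and the note to Fig 1 adds: "Daily cannabis use surveys are sent to each participant for 28 days following enrolment".

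**When treatment starts.** Under Participant timeline, people at V1 "complete a pre-intervention ROC task while EEG activity is recorded, and then receive the first session of tDCS and reappraisal training".

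**What else is measured before treatment.** Baseline measures lists demographics, the CUDIT-R (a screen for misuse over six months) and treatment expectations. Neither that list nor the V1/V5 questionnaires include a daily amount of cannabis. The 5-point rating against typical use belongs to the daily survey, so it too is first asked after V1.

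**Model.** Data analysis names Group, Time and Group x Time as the primary fixed effects, and "multilevel models will be constructed to examine the slopes of longitudinal data across the weeks".

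**The concern.** A reduction needs a starting value, and here every survey is completed after randomised treatment has begun. The other two primary outcomes do not share the gap: the EEG task and the craving questionnaire are both taken at V1 before the first session.

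Two things are at stake. First, the quantity named in the hypothesis is not the one the data can deliver. The data give the level of use after V1 and its trend over four weeks. Second, whatever the first session does by the first survey day falls into the intercept, not the slope. It can then be picked up only by the Group term, which compares arms on the raw level of use. With 30 people per arm, that comparison carries all the person-to-person variation in how much cannabis is used. Chance imbalance in prior use cannot be examined or adjusted for in the same units.

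**Working it through.** The article gives no alpha, power, effect size or SD, so it has no figure of its own to reproduce. The diary length is consistent: 4 weeks x 7 days = 28.

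**Inputs from the article.** 60 participants at 1:1, so n = 30 per arm; survey days 1 to 28.

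**Assumptions (not in the article).** Two-sided alpha 0.05; complete data; between-person SD 1; day-to-day SD 0.7 to 1.0; random-slope SD 0.01 to 0.02 per day; full effect 0.5 or 0.8 SD.

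**Step 1: order of events.** V1 is consent, questionnaires, EEG task, then session 1. The first survey comes after that. It is sent at 8:00 am and looks back 24 hours, so it may reach some hours before the session. Participants must pass a saliva test showing abstinence before each visit, so those hours do not represent usual use.

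**Step 2: what the slope test sees.** With t the centred day, the sum of t² over 28 days is 1,827. For an effect profile e(t), the between-arm slope difference is Σt·e / Σt², with SE = √[(2/30)(slope SD² + day-to-day SD²/1,827)]. The two SE extremes are √[(2/30)(0.0001 + 0.49/1,827)] = 0.00495 and √[(2/30)(0.0004 + 1/1,827)] = 0.00795 per day. Power is by normal approximation.

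| How the effect develops | Slope difference x 27 days, full effect 0.8 SD | Slope power, 0.8 SD | Slope power, 0.5 SD |
|---|---|---|---|
| Complete by day 1, sustained | 0 | 5% | 5% |
| Half-life 2 days | 0.32 | 31–66% | 15–32% |
| Half-life 7 days | 0.61 | 82–99.6% | 43–82% |
| Linear over 28 days | 0.77 | 95% or more | 61–95% |

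A simulation of the first row (20,000 runs, 0.8 SD) rejected in 4.9%, which is alpha.

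**Step 3: what the Group term sees.** For the same immediate 0.8 SD effect, the difference in 28-day means has about 86% power (85% in the simulation). The two terms complement each other: with a 7-day half-life the average effect over the diary is only 0.54 SD, and power of the Group contrast falls to about 54–55%.

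**Step 4: what a baseline would add.** For a 0.5 SD difference in mean use, SE = √[(1 − ρ²) x 2/30], where ρ is the baseline/follow-up correlation and the SD is that of a person's mean. Power is from the noncentral t with 58 df.

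| ρ | Variance factor 1 − ρ² | SE | Power at 0.5 SD |
|---|---|---|---|
| no baseline | 1.00 | 0.258 | 48% |
| 0.3 | 0.91 | 0.246 | 51% |
| 0.5 | 0.75 | 0.224 | 59% |
| 0.7 | 0.51 | 0.184 | 76% |
| 0.8 | 0.36 | 0.155 | 89% |

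By the normal approximation, the difference detectable with 80% power is (1.96 + 0.84) x SE: 0.72 SD without a baseline, and 0.63, 0.52 and 0.43 SD at ρ = 0.5, 0.7 and 0.8.

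**The case against.** The strongest reply is that the trial still has a valid test. Allocation is randomised 1:1 within sex, so the unadjusted Group difference after V1 is unbiased, and chance imbalance is already reflected in its standard error. Group is also a named primary effect, not a fallback. This stands. A reader might infer that an early effect is lost to the analysis; Data analysis does not support that, because only the Group x Time term can miss it.

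Nor is an instantly complete effect the only plausible one. The article describes five weekly sessions and a skill that improves with practice, which suggests a gradual build, and the slopes see much of that. The single-session evidence it cites is for craving, not use, in a study with 8–9 people per condition. This also stands, so the 5% figure describes one boundary case.

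The rating against typical use offers a within-person reference. It is useful as support, but it is a coarse, self-anchored judgement made after treatment began, and it does not measure a prior amount. The CUDIT-R does not fill the gap either, since it is a misuse screen and not a daily amount.

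Finally, the choice of covariates, and which contrast takes precedence, may properly be left to a statistical analysis plan. The article's silence on adjustment is therefore not held against it. The survey schedule is different: the article states it and repeats it, and an analysis plan cannot supply data that were never collected.

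**Conclusion.** The point holds as a mismatch between the stated outcome and the data collected. Reduction from a pre-treatment level cannot be estimated for the first primary outcome; level and trend after V1 can. The between-arm comparison remains valid, and the cost to it is precision. Under the assumptions above, the Group contrast has about 48% power for 0.5 SD without a baseline, against 59–89% with one at correlations of 0.5 to 0.8, and about 51% at 0.3. Those correlations and the effect size are assumed, so the gain is a range and not a forecast. The slope test is blind only to an effect that is complete by the first survey day and then sustained.

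This is a should-fix. It is a pilot with a valid randomised contrast, but its estimates are meant to inform a full-scale trial, and the missing measurement is cheap to obtain beforehand and hard to recover afterwards.

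**What to change.** At V1, after consent and before the first session, collect a retrospective day-by-day record of use (for example 7 or 28 days) with the daily survey's own amount and form items. Enter each person's mean as a baseline covariate in the multilevel model, and read the baseline-adjusted Group term together with Group x Time.

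If no baseline is collected, describe the first primary outcome throughout as level and trend of cannabis use after V1, and drop the word reduction.

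Cost: some added time in a visit already put at about three hours, one covariate, and an amendment through the approval and registry steps described in the Discussion. Recall error is the main drawback: a recalled calendar may correlate less with daily reports than a prospective run-in diary would, which would put the gain towards the lower rows of the range. The article states that recruitment had not begun. For anyone already treated, only later and less reliable recall would be available.

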### Participants

#### Eligibility criteria.

Participants will consist of 60 adults between the ages of 18 and 50 years who reside in the Greater New Haven area in Connecticut, USA and meet criteria for moderate or severe CUD. Diagnostic criteria for CUD will be assessed during screening procedures utilizing a symptom checklist based on the Diagnostic and Statistical Manual for Mental Disorders, 5^th^ Edition (DSM-5) criteria for CUD. Participants must meet at least four of these criteria to be eligible for the study. Additionally, participants must be looking to reduce their cannabis use and must have a positive urine toxicology screen for metabolites indicating regular cannabis use. Participants must also have the capacity to provide informed consent for the study.

Participants may be excluded from the study for several reasons. First, participants may not be receiving any other form of treatment for CUD while they are participating. Lifetime history of serious neurological (e.g., dementia, multiple sclerosis, tumors) or psychiatric (e.g., psychosis, bipolar disorder) conditions, strokes, or losses of consciousness will preclude participants from being eligible. Participants will also be excluded if they have a current medical history of non-CUD substance use disorders. Several contraindications to tDCS will also prevent participants from safely participating, including the presence of metallic implants or electronic devices (e.g., heart pacemakers), any history of seizures, and pregnancy or a plan to become pregnant during the duration of the study. Finally, participants will be excluded for endorsing suicidal or homicidal thoughts, using nicotine equivalent to one pack of cigarettes per day or more, or using exclusionary substances, including amphetamines, benzodiazepines, methamphetamine, cocaine, and opioids. Participants who primarily use cannabis in the form of edibles will be excluded, as the ROC task for CUD utilizes cannabis images related to smoking and vaping and does not include pictures of edibles.

At the start of each visit, the study team will collect biological verification of tetrahydrocannabinol (THC) through urine and salivary toxicology screening. Urine toxicology screening will be completed at each visit to ensure participants meet the full inclusion criteria for the study, in that participants need to both test positive for the presence of THC and negative for exclusionary substances (e.g., opioids, cocaine, methamphetamine). Salivary toxicology screening will be completed at the start of each study visit to ensure that participants abstain from cannabis use prior to each study appointment (i.e., as demonstrated by THC concentration of ≤10 ng/ml). Participants with a positive salivary toxicology screen will be asked to reschedule their visit for another day.

### Recruitment and informed consent

Participants will primarily self-refer to this study through flyers posted in the community, clinical trial listings regularly emailed to a pool of prospective participants through the Yale Center for Clinical Investigation (YCCI), and trial listings on internet resources (e.g., ClinicalTrials.gov). Prospective participants will be screened by a research assistant to determine eligibility. If a participant is eligible, study staff will schedule their first study visit. Participants will receive an electronic copy of the consent form to review prior to their first appointment. Prior to any research data being collected, a research assistant will discuss the study in detail with prospective participants and assess each participant’s capacity to provide informed consent using a brief questionnaire on important details of the study. Once capacity to provide consent is determined, the participant and research team member will sign the consent form, and the participant will be provided a copy for their records. The consent form and questionnaire assessing capacity to provide consent are included as supporting materials. Recruitment has not yet started and is anticipated to take place from April 2025 to April 2026.

### Participant timeline

The timeline for participants is presented in Fig 1. After participant eligibility is determined, participants will be invited to the first study visit (V1), where they will provide informed consent for participation, complete baseline questionnaires, complete a pre-intervention ROC task while EEG activity is recorded, and then receive the first session of tDCS and reappraisal training. Participants will also complete the Marijuana Craving Questionnaire (MCQ) [37] before and after the intervention. This visit should take about three hours.

**Fig 1 pone.0328205.g001:**
[figure not shown]
Notes: AECS: Anticipated Effects of Cannabis Scale; CFCS: Consideration for Future Consequences Scale; CUDIT-R: Cannabis Use Disorder Identification Test, Revised Edition; ERQ: Emotion Regulation Questionnaire; GAD-7: Generalized Anxiety Scale; PHQ-9: Patient Health Questionnaire; MCQ: Marijuana Craving Questionnaire; SRHI: Self-Report Habit Index; ROC task: Regulation of craving task. TDCS: 20 minutes of 1.5mA active/shame transcranial direct current stimulation; TAS-20: Toronto Alexithymia Scale-20; TEX-Q: Treatment Expectations Questionnaire; WHODAS 2.0: World Health Organization Disability Assessment Schedule 2. Note that questionnaire completion and the ROC task with EEG recording occur before the intervention session on V1, and after the intervention session on V5. * Daily cannabis use surveys are sent to each participant for 28 days following enrolment.

Study visits two through four (V2-V4) will be shorter visits during which participants only receive tDCS and reappraisal training and complete the MCQ before and after the intervention. Study visit five (V5) will consist of the same intervention administration and assessment of cannabis cravings as all previous visits. Additionally, participants will complete a post-intervention ROC task while EEG activity is recorded followed by post-intervention questionnaires.

At every appointment, research staff will assess for any adverse events (AEs) and record those reported by each participant in their study record. The study investigators will be responsible for determining the severity of AEs and their relationship to study procedures. Following any severe AEs that are possibly, probably, or definitely related to study procedures, research staff will consult the investigative team to determine if it is appropriate to continue study procedures. Although we do not expect any serious adverse events (SAEs), any participant who reports an SAE will be withdrawn from the trial and referred for appropriate follow-up care. Additionally, following the first study visit and until the end of the last study visit, participants will receive a once-daily survey asking about the amount of cannabis used and the form (e.g., smoked, vaped, edibles) of cannabis used in the past 24-hour window. In this survey, participants will also rate how the amount of cannabis used compares to the amount of cannabis they would typically use.

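### Any SAE removes the participant from the whole trial, so outcome data after the event are lost when only study procedures may need to stop

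*Protocol article*

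**What the plan says.** All the safety rules at issue are in the protocol article under Participant timeline, in the text that follows the Fig 1 notes.

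- **Collection.** "At every appointment, research staff will assess for any adverse events (AEs) and record those reported by each participant in their study record".
- **Judgement.** "The study investigators will be responsible for determining the severity of AEs and their relationship to study procedures".
- **Severe AEs judged at least possibly related.** "research staff will consult the investigative team to determine if it is appropriate to continue study procedures".
- **SAEs.** None are expected, but "any participant who reports an SAE will be withdrawn from the trial and referred for appropriate follow-up care".

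Three other parts of the article determine what withdrawal costs. Under Primary outcomes, daily use comes from a survey link sent each morning, the MCQ is given before and after every session, and the ROC task with EEG is done once before the first session and once after the fifth. Under Data analysis, daily use is analysed in a multilevel model with maximum likelihood for missing values, while EEG, MCQ and ROC craving are analysed by ANOVA. Under Study design, allocation is 1:1; with 60 participants that is 30 per arm.

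**The concern.** Stopping study procedures and leaving the trial are different decisions. The first concerns what is done to the participant, and the second concerns whether outcomes are still measured. The severe-AE sentence speaks only of study procedures, so the authors have the vocabulary for the distinction. The SAE sentence does not use it.

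As a result, an event after randomisation ends measurement even when the participant could and would still give data. The people removed are not a random subset: an SAE may be linked to cannabis use, to general health or, in principle, to the assigned arm. Missing data that arise this way weaken the as-randomised comparison. The daily survey, which is answered remotely and needs neither stimulation nor attendance, would be cut off for no statistical reason.

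**Working it through.** The article states no SAE rate and no power calculation, so there is no figure of the plan to reproduce. The check has three steps.

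**1. The two rules side by side**

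| | Severe AE | SAE |
|---|---|---|
| Relatedness needed? | Yes, at least possible | No |
| Consequence | Consultation | Automatic withdrawal |
| What may stop | Study procedures | The trial |

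The investigators' judgement of relatedness is used in the first rule and not in the second.

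**2. What one withdrawal loses**

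Inputs: 28 daily surveys, and five visits taken as exactly 7 days apart (the article says approximately weekly). Two MCQ scores per visit give 10 in all, and there is one post-baseline ROC/EEG, after the V5 session. With withdrawal at the start of visit k (k = 2 to 5), surveys lost = 28 − 7(k − 1) and MCQ scores lost = 2(6 − k).

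| Withdrawn at start of | Surveys lost | MCQ scores lost | Post-baseline EEG/ROC |
|---|---|---|---|
| V2 | 21 | 8 | lost |
| V3 | 14 | 6 | lost |
| V4 | 7 | 4 | lost |
| V5 | 0 | 2 | lost |

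All 28 surveys are lost only if withdrawal comes before the first one is answered. Reports given before the event stay in the daily-use model. For EEG and ROC craving, a participant with V1 alone carries no information on change from V1 to V5.

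**3. How often, and how much precision**

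The SAE risk per participant, p, over the study is an assumption.

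- Expected number = 60p: 0.3 at p = 0.005 and 0.6 at p = 0.01.
- P(at least one) = 1 − (1 − p)^60: 1 − 0.995^60 = 26%; 1 − 0.99^60 = 45%.
- One participant as a share of an arm: 1/30 = 3.3%.

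Detectable standardised difference = (1.960 + 0.842) × √(1/n₁ + 1/n₂), as an illustration with two-sided alpha 0.05, 80% power and a two-sample normal approximation, all assumed:

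| Assumed loss to SAEs | Participants lost | Detectable d | Power at d = 0.723 |
|---|---|---|---|
| 0% | 0 | 0.723 | 80.0% |
| 1% | 0.6 | 0.727 | 79.6% |
| 5% | 3 | 0.742 | 77.9% |
| 10% | 6 | 0.762 | 75.7% |

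If one arm alone loses one participant (30 against 29), d = 0.730. Power is therefore not the issue. What remains is that the loss is selective and could be avoided.

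**The case against.** The strongest reply is that SAEs are not expected in a pilot of 60 lasting about four weeks, that maximum likelihood keeps the earlier daily reports, and that a journal article condenses a fuller protocol. The first two parts stand and limit the size of the point. The third does not remove it, because the article states the rule and states it as withdrawal from the trial.

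Three stronger readings are tempting, and the document supports none of them.

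- **A reader might infer that the two event rules contradict each other.** Under them, a severe AE definitely related to stimulation leads to a consultation, while an unrelated SAE leads to automatic removal. But severe and serious are different categories, and both rules can be followed. The ordering is odd enough for the authors to confirm that it is intended, and no more than that.
- **A reader might infer that safety follow-up ends.** AEs are described as assessed at appointments, which withdrawal would end. The article does not say that this is the only route, it provides referral for follow-up care, and tracking an SAE to its outcome is commonly left to the full protocol. The loss of safety data is not shown.
- **A reader might infer that the comparison is biased by arm.** Nothing in the article indicates different SAE rates under active and sham stimulation, or that participants will not be analysed as randomised. Arm-related missingness is a possibility only.

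**Conclusion.** The point holds as a modest one. The SAE rule, as worded, ends outcome collection together with study procedures and takes no account of relatedness. Data after the event are lost: the remaining daily surveys and MCQ scores and, for any SAE before V5, the sole post-baseline EEG/ROC measurement. Data from before the event are not lost to the daily-use model.

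The expected size is small. It rests on an assumed SAE risk, since the document gives none: at 0.5% to 1%, less than one participant is expected to be affected, and the detectable difference moves from 0.723 to at most 0.727. The 26% to 45% is the chance that the rule is used at all and does not measure bias. The reason to act is that the missingness is selective and cheap to prevent.

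**What to change.** Reword the SAE sentence so that stopping study procedures is distinct from leaving outcome assessment. State that, after an SAE:

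1. participants who are willing and able are asked to continue the daily surveys and to complete the V5 outcome assessments;
2. the outcome of the SAE is recorded;
3. the participant is analysed in the arm to which they were randomised.

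The authors should also check that the SAE sentence and the severe-AE sentence before it are reconciled as intended. Which stopping rule is right is for them to decide.

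**Cost.** Mainly wording, because the surveys and V5 are already planned and compensated. There are three downsides. The post-intervention ROC/EEG is defined as following the fifth session, so the text must allow a V5 measurement from someone who did not have all five sessions. The MCQ is tied to the sessions, so its missed before-and-after pairs cannot be recovered. If the change counts as a major amendment, the Discussion requires funder preauthorisation, ethics committee approval and a registry update. The Intervention section also permits unblinding after a related AE; if that happens, its date should be recorded so that later self-reports can be identified.
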